### Follow-up visits

A follow-up visit will be carried out just before each session of the POTs and active control interventions (the schedule for which is shown in Figure 4). During the follow-up visit, the participant will complete self-report questionnaires measuring postural awareness (the Postural Awareness Scale) and perceived stress (Cohen’s Perceived Stress).

Participants who suffer a fall trauma during the course will attend an additional follow-up visit, which will take place on the day of the injury. The military medic, or one of his or her assistants, will collect medical information relating to the trauma, and carry out a posturography measurement. The participant will then complete questionnaires measuring postural awareness (the Postural Awareness Scale) and perceived stress (Cohen’s Perceived Stress).

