| Schedule | The study will consist of the following visits:   - 1 inclusion visit: inclusion interview and written consent - 1 initial assessment visit: self-report questionnaires (medico-biographical, postural awareness (Postural Awareness Scale) and stress (Cohen’s Perceived Stress Scale), clinical and paraclinical posture measurements and saliva collection. - 4 follow-up visits carried out at the start of the POT or active control sessions, consisting of: self-report questionnaires (postural awareness and perceived stress), - there will be 1 additional visit for participants who suffer a fall-related trauma during the course. The participant will complete questionnaires measuring postural awareness and perceived stress, and a posturography measurement will be performed. - 1 end-of-study visit will take place on the day following the last session of the POT or the active control, or on the day of the fall injury if it occurs before the end of the POT or active control intervention. This visit will include: paraclinical measurement of posture, self-report questionnaires (postural awareness and perceived stress) and saliva collection. |
| Number of subjects | The sample should include 200 participants in each of the two groups (POT and active control), making a total of 400 participants. |

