### The intervention

The POTs intervention will consist of practical courses run by the designated POTs instructor in each military unit. This person is a member of the military who has completed the POT trainer course delivered by the French Centre National des Sports de Défense. The intervention is divided into six, one-hour sessions, spread over three weeks, with two sessions per week. The first two sessions will be scheduled at the start of the selection course (ideally the day before it begins).

The intervention will include theoretical instruction and practical exercises in POTs that have been identified as useful in increasing body awareness (paying attention to breathing, muscle relaxation, mental imagery). The contents of the six sessions will be established and validated beforehand by POTs instructors from the six military units, under the supervision of the POTs instructor who coordinates the intervention.

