# EVALUATION CRITERIA

## Primary endpoint

The primary endpoint will be the rate of fall injuries following a loss of balance in each of the two groups (POTs *vs.* active control).

A fall injury will be recorded by the medic responsible for providing healthcare during the selection course. The injured participant will be required to attend an additional follow-up visit on the same day after the initial medical consultation.

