### End-of-study visit

Participant follow-up will end either: (*i*) on the day following the last session of the POTs or the active control intervention; or (*ii*) the day they leave the course (for whatever reason), if this occurs before the end of the intervention (POTs or active control).

A posturography measurement will be performed by the military medic, or one of his or her assistants, and the participant will complete questionnaires measuring postural awareness (the Postural Awareness Scale) and perceived stress (Cohen’s Perceived Stress). Finally, a 4 ml saliva sample will be collected.

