## End of the study

### Discontinuation criteria for a participant

Participation will end:

- After the last session of the intervention (POTs or active control),
- On leaving the course (for whatever reason) if this occurs before the end of the intervention.

It will not be possible for a participant who leaves to re-join the program at a later date.

There are no exclusion criteria in the protocol.

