# LOGISTICS

## General logistics

The coordinating investigator, with the help of her scientific collaborator, will supervise all study visits (see paragraph 6.2). For inclusion and initial evaluation visits, the coordinating investigator and her scientific collaborator will be assisted by medical staff (physicians, nurses and stretcher-bearers) in the respective military unit. Follow-up visits will be carried out prior to each intervention session (POTs or active control) by the POTs instructor. The additional follow-up visit (carried out if the participant suffers a fall trauma during the study period) and the end-of-study visit will be conducted by the unit’s medical officer or one of his or her collaborators.

The coordinating investigator will also be responsible for monitoring progress, checking that progress reports are prepared, and that Case Report Forms are updated (requests for additional information, corrections, etc.).

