# STATISTICAL ASPECTS

## Calculating the number of subjects required

To date, there are no data in the literature on the effectiveness of POTs in preventing sports-related injuries. However, discussions with military unit managers and medical officers suggest that a reduction in the injury rate of around 15% would be clinically relevant. Preliminary epidemiological data from the various units indicates that the rate of fall injuries is around 50%.

To determine the sample size required to observe a significant difference in rates between the two groups, we used the following parameters:

- statistical test: two-tailed
- fall rate in the active control group: 50%
- fall rate in the POTs group: 35%
- statistical significance = 0.05
- power = 0.80

Taking into account potential drop-outs (estimated at 10%), the sample should consist of 200 participants per group, for a total of 400 participants over the two years of the study.

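### The summary and the body of the protocol set different days for an injured participant's end-of-study posturography, so injury-day recordings can enter the POTs pre/post comparison; the recording also lacks a fitness-to-stand condition (minor)

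*Protocol*

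**What the plan says.** **When the end-of-study visit takes place.** The Research summary (Schedule) places it on the day after the last session, "or on the day of the fall injury if it occurs before the end of the POT or active control intervention". The section End-of-study visit also gives the day after the last session, but its alternative is "the day they leave the course (for whatever reason), if this occurs before the end of the intervention". Discontinuation criteria for a participant agrees with that section: "On leaving the course (for whatever reason) if this occurs before the end of the intervention". Neither of these two sections names an injury as a trigger. Posturography is part of the visit in both the summary and the body.

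**What happens on the day of an injury.** Primary endpoint states: "The injured participant will be required to attend an additional follow-up visit on the same day after the initial medical consultation". Follow-up visits then says: "The military medic, or one of his or her assistants, will collect medical information relating to the trauma, and carry out a posturography measurement". General logistics gives this visit and the end-of-study visit to the unit's "medical officer or one of his or her collaborators". Para-clinical parameters describes the test as static balance on a platform with eyes closed, and says that a standard procedure for it will be put in place.

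**How the recordings are used.** Analysis of secondary objectives compares posturography before and after the intervention as paired means, in the POTs group only. Statistical methods replaces missing data by the group mean of the variable. It also foresees a flow chart showing subjects left out of the analysis, with reasons.

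**The concern.** The paired comparison is meant to show what POTs do to postural balance. It needs one defined post-intervention recording per participant. For someone who is injured and stays on the course, the summary gives a recording on the injury day and the body gives a later one. A recording taken hours after a fall mixes the effect of the injury with the effect of the training. The comparison has no control arm that could separate the two.

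The sessions are "spread over three weeks, with two sessions per week", so a participant injured before session 3 has had at most two of the six. Under the summary, that participant's injury-day recording would be the post value.

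If the injury prevents a recording, the stated missing-data rule inserts the group mean. The gap disappears from the analysis and the standard error is too small.

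There is also a secondary safety point. The protocol classes all its measurements as research (The distinction between care and research) and identifies no individual risk (Risks). Yet it orders a standing test on the day of a fall injury without saying when the test should not be done.

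**Working it through.** **1. The two triggers side by side**

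| Participant injured before the last session | Research summary | End-of-study visit and Discontinuation criteria |
| --- | --- | --- |
| leaves the course that day | injury day | injury day |
| leaves later, before the last session | injury day | day of leaving |
| completes all sessions | injury day | day after the last session |

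The texts conflict in rows 2 and 3. Row 1 is an injury-day value under either text.

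Biological sample collection codes the final visit Vfin and additional visits Vadd1, Vadd2 and so on. These are sample labels, but they treat additional visits as repeatable and distinct from the final one. That fits the body, so the summary clause is the outlier. The summary also lists the injury visit and the end-of-study visit separately, each with posturography, so two recordings could fall on one day.

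**2. How many participants**

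Inputs from Calculating the number of subjects required: "fall rate in the POTs group: 35" (per cent), control rate 50%, two-sided 5%, power 80%, 10% drop-out, 200 per group. The stated size reproduces with the continuity-corrected two-proportion formula: 183 per group, then 183/0.9 = 204 or 183 × 1.1 = 202. Without the correction it is 170, then 189.

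- Injured POTs participants: 0.35 × 200 = 70, or 0.35 × 180 = 63 after drop-out.
- This counts all injured participants, rows 1 to 3 together. The protocol does not give the split, so the number in conflict is between 0 and about 70.

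**3. Effect on the paired comparison**

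Assumptions: 180 pairs, SD 1 at each time, pre/post correlation r, and an injury-day worsening of x SD in a share s of post values. The mean change then shifts by s·x.

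Detectable change = 2.80 × √(2(1−r)) / √180. The worsening that cancels it is that value divided by s.

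| r | detectable change (SD) | cancelled at s = 0.35 | cancelled at s = 0.10 |
| --- | --- | --- | --- |
| 0.3 | 0.247 | 0.71 | 2.47 |
| 0.5 | 0.209 | 0.60 | 2.09 |
| 0.7 | 0.162 | 0.46 | 1.62 |

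The share s = 0.35 is the ceiling, reached if the summary is followed and the 35% applies to the three weeks.

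With no true effect, 180 to 200 pairs and an assumed shift of 0.25 to 1.0 SD of the change score, the paired test rejects in about 6% to 27% of trials at s = 0.10, and in about 21% to 99% at s = 0.35. If injury worsens balance, these rejections point to worse balance after POTs.

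**4. Effect of mean filling**

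Let f be the filled share of post values, with values missing at random.

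- Variance of the mean change as computed from filled data: [1 + (1−f) − 2(1−f)r]/n
- True variance: [1/(1−f) + 1 − 2r]/n
- Ratio of the two: 1 − f for any r, so the standard error is multiplied by √(1−f).
- Actual two-sided error: 2 × (1 − Φ(1.96·√(1−f))).

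| assumed share of injured not recordable | f = 0.35 × share | SE multiplied by | actual error at nominal 5% |
| --- | --- | --- | --- |
| 10% | 0.035 | 0.98 | 5.4% |
| 25% | 0.0875 | 0.96 | 6.1% |
| 50% | 0.175 | 0.91 | 7.5% |

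Simulation (20,000 runs per setting; r = 0.3, 0.5, 0.7) gave 7.0%, 7.4% and 7.6% at f = 0.175, and 4.8% to 5.0% with nothing filled. Missing at random is a convenience here, since the stated cause of missingness is the injury.

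**The case against.** The body sections agree with each other and with the visit codes, so a site following them has a defined day. The conflict comes from one clause in a summary table. This stands, and it is why the point is a wording mismatch and not an undefined endpoint.

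A reader might infer that up to 70 post values are in dispute. The documents do not support that: 70 is a headcount of all injured participants, the texts coincide for those who leave on the injury day, and the sample-size section does not tie its rates to the three weeks. The course can run beyond them, since the fourth secondary objective follows participants to its end.

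A reader might also infer that contamination could manufacture a POTs benefit. A worsening on the injury day acts the other way.

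On safety, a stronger reading is that injured participants are made to stand regardless of their condition. The text does not say so. The visit follows a medical consultation, medical staff run it, participants may withdraw at any time, and the standard posturography procedure, which is not shown, may hold stopping criteria. The statement that acute trauma typically involves the lower limbs concerns the marine commando course; for the other units the protocol does not give injury site. What remains is that this protocol sets a sequence, consultation then visit, and not a condition.

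Mean replacement is a general rule, and analysis-set details may sit in an analysis plan. But the rule is fixed in the protocol, and nothing there exempts these values.

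**Conclusion.** The point holds as a minor one. The summary contradicts the body for participants injured before the last session who do not leave that day: 0 to at most about 70 of 200 POTs participants, assuming the 35% rate applies to the three weeks. Correcting the summary does not remove every injury-day value, because those who leave on the injury day still contribute one.

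The likely direction is to mask a POTs benefit on balance. The size depends on the share affected and on the injury-day shift, neither of which the protocol gives. Mean filling adds a modest understatement of the standard error, 2% to 9% under the assumed shares. The missing fitness condition is a secondary safety point.

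The point is limited to the posturography criterion of the first secondary objective. A reader might extend it to the primary result, but the survival analysis needs the date of the fall injury, which is recorded under either text. The sample size does not use posturography, and the prediction model uses measurements taken before the activities begin.

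**What to change.** - In the Research summary, replace the injury-day trigger with the day of leaving the course, as in End-of-study visit and Discontinuation criteria.
- In Follow-up visits and End-of-study visit, do posturography on an injured participant only if the examining medic clears him or her to stand. Let one recording serve both visits when they coincide.
- Add a case report form entry for posturography not done because of injury, and state in Statistical methods that mean replacement does not apply to these values.
- Report the paired posturography comparison with and without injury-day values, and label the second as restricted to participants not acutely injured.

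The cost is a few sentences of protocol wording, one form entry and one extra table. There are two downsides. Some injury-day recordings will be lost. The restricted comparison is selected on the primary outcome, so it should be read only as a companion to the full one.

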### End-of-study visit

Participant follow-up will end either: (*i*) on the day following the last session of the POTs or the active control intervention; or (*ii*) the day they leave the course (for whatever reason), if this occurs before the end of the intervention (POTs or active control).

A posturography measurement will be performed by the military medic, or one of his or her assistants, and the participant will complete questionnaires measuring postural awareness (the Postural Awareness Scale) and perceived stress (Cohen’s Perceived Stress). Finally, a 4 ml saliva sample will be collected.

## End of the study

### Discontinuation criteria for a participant

Participation will end:

- After the last session of the intervention (POTs or active control),
- On leaving the course (for whatever reason) if this occurs before the end of the intervention.

It will not be possible for a participant who leaves to re-join the program at a later date.

There are no exclusion criteria in the protocol.

### Early termination of the experimental procedure by the participant

All participants may withdraw from the study at any time, for any reason. In the event of early termination, data collected up to the date of withdrawal of consent may be used, unless the participant objects, in accordance with article L 1122-1-1 of the French Public Health Code. Participants who withdraw will not be replaced.

### Study discontinued by the sponsor

The sponsor may end the study at any time, for the following reasons:

- Inability of the investigator to include subjects on the planned schedule.
- No written consent.
- Major breaches of protocol.
- Incomplete or erroneous data.

The sponsor will draw up an end-of-trial declaration within 90 days of the end of the study.

If the clinical trial ends (definitively) earlier than planned, a declaration must be submitted to the ANSM and the Institutional Review Board within 15 days, giving the reasons for the decision.

### Study discontinued by the investigator

In the event of an adverse event that the investigator deems severe and likely to jeopardize the health of subjects, he or she may end the study in agreement with the sponsor.

## Research-related constraints and compensation for subjects

Participants may not simultaneously take part in another research project. No compensation will be given.

## Research schedule

- Duration of inclusion: 24 months
- Duration of the intervention: 3 weeks
- Duration of each participant’s participation: 4 weeks
- Total study time: 25 months

# LOGISTICS

## General logistics

The coordinating investigator, with the help of her scientific collaborator, will supervise all study visits (see paragraph 6.2). For inclusion and initial evaluation visits, the coordinating investigator and her scientific collaborator will be assisted by medical staff (physicians, nurses and stretcher-bearers) in the respective military unit. Follow-up visits will be carried out prior to each intervention session (POTs or active control) by the POTs instructor. The additional follow-up visit (carried out if the participant suffers a fall trauma during the study period) and the end-of-study visit will be conducted by the unit’s medical officer or one of his or her collaborators.

The coordinating investigator will also be responsible for monitoring progress, checking that progress reports are prepared, and that Case Report Forms are updated (requests for additional information, corrections, etc.).

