### The active control

The active control will unfold in the same way as the POTs intervention: there will be six one-hour sessions, spread over the three weeks of the study, with two sessions per week. These sessions will consist of exercises (details of the sessions are available in APPENDIX 2 ) that focus on high-level cognitive processes such as reasoning, information processing and creativity. They will be divided into two p3arts: the first, theoretical component will describe the processes that will be the focus of the session, and the second, practical component will focus on exercises.

These sessions will be carried out under the supervision of the person responsible for the POTs intervention that will take place the following year (the POTs instructor).

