## Data collection methods

A paper-based Case Report Form will be created for the study.

The person(s) responsible for maintaining Case Report Forms must be clearly identified in the task allocation document. Each Case Report Form will be strictly anonymous and labelled using the participant’s identification number. During the study, or when it ends, the data collected and transmitted to the sponsor by the persons directing and supervising the research (or any other specialist) will be anonymized. Under no circumstances can the names or addresses of the persons concerned appear in clear text.

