## Data access and confidentiality

The sponsor is responsible for obtaining the agreement of all parties involved in the study in order to guarantee direct access to all study locations, source data, source documents and reports needed for quality control and audit purposes.

The persons directing and supervising the study will make any documents and individual data that are essential for monitoring, quality control and auditing the study available to persons authorized to access these documents in accordance with the legislative and regulatory provisions in force.

In accordance with current legislation, in particular Articles L.1121-3 and R.5121-13 of the French Public Health Code, persons with direct access to source data (for example, investigators, quality control personnel, instructors, clinical research assistants, auditors and any other persons called upon to collaborate in the trials) will take all necessary precautions to ensure the confidentiality of information relating to the study, and those who participate, notably their identity, and the results obtained. These persons, together with those directing and supervising the study, are bound by the conditions of physician–patient privilege.

During, or at the end of the study, individual data that is collected and reported to the sponsor by the persons directing and supervising the study (or any other specialized parties) will be codified. Under no circumstances should the names or addresses of the persons concerned appear in plain text.

Participants will be coded as follows: unit code (GIGN – GI, CPA 10 – CP, 1^ier^ RPIMA –RP, 13^ième^ RDP –RD, ECOFUS – EC, BSPP – BS); a number indicating the order of inclusion in the unit; the first letter of the participant’s surname and first name.

The sponsor will ensure that each person involved in the study has been informed about access to personal data, which is essential for quality control purposes.

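### The mid-course stress and postural-awareness questionnaires are taken by the instructor who delivers the programme, with no stated safeguard, and the within-POTs analysis cannot separate a reporting shift from the effect of time

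*Protocol*

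**What the plan says.** All references are to the Protocol.

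- **Delivery.** Under The intervention: "The POTs intervention will consist of practical courses run by the designated POTs instructor in each military unit". Under The active control: "These sessions will be carried out under the supervision of the person responsible for the POTs intervention that will take place the following year". The same role therefore serves both years.
- **Collection.** Under General logistics: "Follow-up visits will be carried out prior to each intervention session (POTs or active control) by the POTs instructor". The Follow-up visits section makes PAS and PSS the content of these visits, and the Para-clinical parameters section has them completed on paper.
- **Other time points.** The Initial evaluation visit is run by the investigator or a collaborator. General logistics gives the end-of-study visit and the extra visit after a fall injury to the unit's medical officer or a collaborator.
- **Analysis.** Under Statistical methods, PAS and PSS are compared across six measurement times by repeated-measures ANOVA, for the POTs group.
- **Anonymity and access.** Data collection methods states: "Each Case Report Form will be strictly anonymous". Data access and confidentiality builds the participant code from the unit, the order of inclusion and "the first letter of the participant’s surname and first name". It also names instructors among those with direct access to source data, under a duty of confidentiality. Data flow limits access to the consolidated data to investigators and collaborators. Biological sample collection uses a subject code of unit plus subject number, without initials.

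**The concern.** In the POTs year the instructor teaches breathing, whole-body awareness and stress control (Appendix 2). PAS and PSS ask about closely related things. Participants know which programme they are in and are told the study's objective at inclusion. They complete the forms at a visit run by the trainer, just before the trainer's session. Some may report more awareness or less stress than they would to a neutral collector.

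PAS and PSS carry the self-report part of the two mechanistic objectives, namely that POTs act through postural awareness and through a lower stress response. A reporting shift over the course would look like the mechanism at work. Analysis cannot remove it afterwards, so the safeguard has to be in place before collection starts.

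**Working it through.** **1. Who collects what, over time**

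| Time point | PAS/PSS taken at a visit run by |
| --- | --- |
| Baseline | Investigator's team |
| Pre-session visits | POTs instructor |
| After a fall injury (if any) | Unit medical officer or collaborator |
| End of study | Unit medical officer or collaborator |

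**2. Share of scheduled times taken by the instructor**

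- The Schedule in the Research summary gives 4 follow-up visits: 1 + 4 + 1 = 6, which reproduces the six measurement times of the analysis section. Share: 4/6 = 67%.
- The Follow-up visits section places a visit before each session, and there are six sessions: 1 + 6 + 1 = 8. Share: 6/8 = 75%.

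The two counts do not agree, but on either one the instructor takes most of the scheduled points.

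**3. What the planned test can separate**

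The ANOVA tests for change over time within one group. Collector is tied to time in that group: investigator's team first, instructor in the middle, medical officer last. A collector effect, or a shift that grows as participants learn what the programme is meant to do, therefore enters the time effect directly. The stated PAS and PSS analyses include no control-group contrast that could absorb part of it.

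**4. Illustration of size (assumptions, not protocol figures)**

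The documents give no standard deviation, correlation or bias size for PAS or PSS. Assume:

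- 180 analysed POTs participants (200 × 0.90, using the protocol's 10% drop-out);
- no true change;
- a pure reporting shift of *b* standard deviations between two times, for example baseline and one instructor-run visit;
- a correlation *r* of 0.5 to 0.7 between the two times.

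For a paired comparison, the noncentrality is λ = b·√180 / √(2(1 − r)). The chance of p < 0.05 is Φ(λ − 1.96) + Φ(−λ − 1.96).

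| b | r | λ | Chance of p < 0.05 |
| --- | --- | --- | --- |
| 0.1 | 0.5 | 1.34 | 27% |
| 0.1 | 0.7 | 1.73 | 41% |
| 0.2 | 0.5 | 2.68 | 77% |
| 0.2 | 0.7 | 3.46 | 93% |

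The protocol plans an ANOVA over six times, not this two-time test, so the figures show only the order of magnitude. At this sample size a small shift is enough to matter.

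**5. Anonymity and access**

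Forms labelled with a code that contains a unit, an inclusion number and two initials are not strictly anonymous. The saliva code shows that the study can work without initials. The section opening Data collection and processing counts paper questionnaires as source documents. Listing instructors among those with direct source-data access therefore reaches PAS and PSS, while Data flow draws the access limit more narrowly.

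**The case against.** The strongest reply is that the exposure is limited. The pre- and post-intervention scores are not taken by the trainer, and if the first follow-up visit precedes session 1 it also precedes any POTs teaching. The forms are self-completed in a study declared open, and those with source access are bound to confidentiality. Posturography and saliva are separate criteria for the same objectives. All of this stands, and it keeps the point to the mid-course self-reports of two secondary objectives. It does not answer the planned ANOVA, which includes those mid-course points and has collector confounded with time. Even from baseline to end of study, the collector changes.

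Three stronger readings are tempting, and the documents do not support them.

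- **A bias that differs between the two years.** The same instructor role serves both. The control content is not wholly unrelated either: Appendix 2 includes sensory channels, coping strategy and mental imagery. A stronger pull in the POTs year is plausible, but no between-year PAS or PSS test is stated for it to distort.
- **Under-reporting of stress because of selection.** Participants are selection candidates, but nothing gives the instructor a part in selection or says that selectors see the answers.
- **Initials as the cause.** Sessions are taught in groups of at most 20 to 25, so the instructor may well know who is who with or without initials. Removing them settles the anonymity conflict but does not cure a demand effect. That the questionnaires themselves bear the initials is inferred from the labelling rule and the code.

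**Conclusion.** The point holds as a risk of reporting bias in the mid-course PAS and PSS: 4 of 6 scheduled times, or 6 of 8 on the other visit count. It matters because the stated analysis is within the POTs group, where a reporting shift or change of collector cannot be told apart from the time effect. Under the assumptions shown, a shift of 0.1 SD would give a false significant result in 27% to 41% of paired comparisons, and 0.2 SD in 77% to 93%. Neither the presence nor the size of a shift can be derived from the documents, so the endpoints should not be described as biased. The primary endpoint is untouched, because fall injuries are recorded by the course medic.

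The conflict between strictly anonymous forms and a code with initials is a separate inconsistency, and it stands regardless of any bias. Together these justify a cheap correction rather than a change of design.

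**What to change.** - In Follow-up visits and General logistics, state that participants complete PAS and PSS alone and return them sealed, that the instructor neither sees nor handles completed forms, and that the forms go unopened to IRBA, where the study data are processed. State also that participants are told their answers do not reach the unit or selection staff.
- In Data access and confidentiality, drop the initials so that the participant code matches the unit-plus-number code used for saliva.
- Reconcile Data collection methods, Data flow, and Data access and confidentiality on what anonymous means and on whether instructors may see questionnaires.

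The cost is envelopes or a locked box and a short amendment, with no extra visits. The real loss is that the instructor can no longer check forms for blanks on the spot. That deserves some thought, because the protocol replaces missing values with the group mean. A printed reminder on the form to check every item before sealing would recover part of it.
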